## Abstract

**Background:**

Insufficient physical activity and prolonged sedentary behavior among college students are associated with reduced lower-limb muscle strength, impaired dynamic balance, and increased susceptibility to sports-related knee injury. Female college students may be especially vulnerable because of sex-specific neuromuscular and biomechanical characteristics. Tai Chi Chuan may improve proprioceptive control and coordinated knee muscle activation, whereas unstable resistance training may rapidly enhance strength and neuromuscular stabilization. Whether a combined programme can produce complementary central-peripheral benefits remains to be verified in a rigorously designed randomized trial.

**Methods:**

This protocol describes a single-center, parallel-group, randomized controlled trial. Fifty-seven healthy female college students aged 18–22 years will be recruited from Fenyang College, Shanxi Medical University, and randomly allocated in a 1:1:1 ratio to a Tai Chi Chuan group (TCC), unstable resistance training group (URT), or Tai Chi Chuan combined with unstable resistance training group (T + URT). All interventions will last 8 weeks, with three 60-min sessions per week. The primary outcomes will be dominant-leg knee extensor peak torque, knee flexor peak torque, and hamstring-to-quadriceps ratio measured using an isokinetic strength testing system at 60 degrees/s. Secondary outcomes will include overall stability index, anteroposterior stability index, and mediolateral stability index under eyes-open and eyes-closed conditions measured with the Biodex Balance System. Assessments will be conducted at baseline and after the 8-week intervention. Intention-to-treat and per-protocol analyses will be used. Missing data will be handled using multiple imputation where appropriate.

**Discussion:**

This trial is designed to determine whether Tai Chi Chuan combined with unstable resistance training provides superior improvements in knee muscle function and dynamic balance compared with either intervention alone.

**Trial registration:**

https://itmctr.ccebtcm.org.cn, Identifier (ITMCTR2026000456).

## Introduction

The decline in physical fitness among university students has become an important public health concern. Reduced skeletal muscle strength, impaired endurance, and diminished balance control are frequently associated with insufficient physical activity and prolonged sedentary behavior (1–3). These changes are particularly relevant in female college students, in whom lower-limb muscle strength and dynamic balance are essential for daily mobility, safe participation in sport, and prevention of knee injury during rapid postural transitions (4, 5). Thus, improving these functional parameters is a critical intermediate target toward lowering the actual incidence of knee injuries in this sedentary population.

Female students may face a higher risk of lower-limb functional impairment because of biomechanical and neuromuscular characteristics that influence knee loading, postural control, and injury susceptibility. Weakness or imbalance between the knee extensors and flexors can compromise joint stability. The hamstring-to-quadriceps ratio (H/Q) is commonly used to reflect the balance between the agonist and antagonist muscle groups around the knee. A more balanced H/Q ratio may contribute to better joint control during movement and may reduce the risk of excessive anterior tibial translation and related knee injuries (6–8).

Dynamic balance is another key determinant of lower-limb functional performance. It requires the integration of visual, vestibular, proprioceptive, and neuromuscular inputs. Under eyes-open conditions, balance performance depends partly on visual feedback, whereas eyes-closed conditions place greater demand on proprioceptive and vestibular control. Exercise strategies that simultaneously improve strength and proprioceptive integration are therefore likely to produce stronger functional benefits than strategies targeting only one component (9–11).

Tai Chi Chuan is a traditional mind–body exercise characterized by slow continuous movements, controlled breathing, alternating weight shifting, semi-squat postures, and sustained attentional regulation. These features may activate the muscles surrounding the knee and enhance proprioceptive awareness. The 24-form simplified Tai Chi Chuan routine is widely used in community and university settings because it is structured, feasible, and safe. However, Tai Chi Chuan is generally a low-to-moderate intensity training modality, and substantial improvements in absolute muscle strength may require prolonged practice (12–14).

Unstable resistance training is a strength-oriented modality performed under unstable surface conditions, such as balance pads or wobble boards. By requiring participants to maintain postural control while performing resisted or bodyweight movements, this training may activate deep stabilizing muscles, improve neuromuscular control, and increase lower-limb strength (15). Compared with stable resistance training, unstable resistance training may be especially relevant for balance-related outcomes (16). Nevertheless, resistance exercises based mainly on squats, lunges, and heel raises may preferentially stimulate the extensor chain and may not fully correct flexor-extensor imbalance (17).

Despite increasing research on Tai Chi Chuan and unstable resistance training, critical knowledge gaps remain: most studies focus on single interventions rather than their combined synergistic effects (18, 19); related work has explored Tai Chi Chuan with instability or core training, but to our knowledge, no three-arm RCT have examined Tai Chi Chuan combined with unstable resistance training in young sedentary female college students; existing evidence is largely based on female athletes or older adults with distinct neuromuscular and fitness profiles (20); and few head-to-head comparisons between single and combined interventions exist to guide optimal exercise prescription. Therefore, this combined intervention represents a novel complementary model: Tai Chi Chuan improves central sensory integration, proprioception and agonist–antagonist coordination, while unstable resistance training enhances peripheral muscle stimulation and strength gains, acting via a central–peripheral mechanism. This randomized controlled trial protocol was designed to fill these gaps and test this hypothesis (18, 20).

## Objectives and hypotheses

The primary objective is to evaluate the effects of an 8-week Tai Chi Chuan combined with unstable resistance training programme on knee flexor and extensor strength in female college students, compared with Tai Chi Chuan alone and unstable resistance training alone.

The secondary objective is to compare the effects of the three intervention modalities on dynamic balance capacity under eyes-open and eyes-closed conditions.

The main hypothesis is that the combined intervention will produce greater improvements in knee flexor peak torque, knee extensor peak torque, H/Q ratio, and dynamic balance indices than either single-modality intervention. A secondary hypothesis is that Tai Chi Chuan alone will show particular advantages in proprioception-dependent balance and H/Q optimization, while unstable resistance training alone will show particular advantages in rapid improvement of extensor strength.

## Methods

### Study design and setting

This is a single-center, parallel-group, randomized controlled study protocol. Participants will be recruited from female undergraduates enrolled at Fenyang College, Shanxi Medical University, China. Eligible participants will be randomly allocated into one of three groups: Tai Chi Chuan group (TCC), unstable resistance training group (URT), or Tai Chi Chuan combined with unstable resistance training group (T + URT).

The trial will follow the principles of the Declaration of Helsinki and the Standard Protocol Items: Recommendations for Interventional Trials (SPIRIT). The study will be conducted in the university training venue and laboratory assessment rooms. All outcome measurements will be performed by trained assessors who are blinded to group allocation. Figure 1 displays a flow diag.

**Figure 1 fig1:**
[figure not shown]
CONSORT 2025 flow diagram.

### Participants

Healthy female college students will be recruited through the optional martial arts course and university announcements. Interested students will undergo eligibility screening and will provide written informed consent before enrolment (Table 1). Participants will be asked to maintain their usual diet and lifestyle during the study and to avoid initiating additional structured exercise programmes outside the assigned intervention.

**Table 1 tab1:** Eligibility criteria for study participants.

Eligibility domain	Criteria
Inclusion criteria	Female college students aged 18–22 years; normal physical examination; no history of heart, brain, or kidney disease; no recent sports injury; no regular exercise in the previous 3 months; ability and willingness to complete all tests and training; written informed consent; agreement to maintain usual diet and lifestyle.
Exclusion criteria	Abnormal body morphology or obvious limb defects that may affect testing; fracture, muscle injury, or comparable injury within the past 6 months; inability to complete the intervention because of leave, internship, transfer, or similar objective reasons; inadequate training attendance; poor compliance; any adverse condition judged by investigators to increase exercise risk.
Withdrawal criteria	(R1 Q4)Voluntary withdrawal; repeated non-attendance (defined as missing two consecutive training sessions or three cumulative training sessions); development of a condition that makes further participation unsafe (defined as the occurrence of acute exercise-related injury, severe joint pain, cardiovascular discomfort, dizziness, vomiting, or any other health problem judged by the investigator to preclude safe continued training); investigator decision based on participant safety.

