### Randomization and allocation concealment

After baseline assessment, eligible participants will be randomly assigned to three groups (Tai Chi Chuan group (TCC), unstable resistance training group (URT), or Tai Chi Chuan combined with unstable resistance training group (T + URT)) in a 1:1:1 ratio using simple randomization. The randomization sequence will be generated by an independent statistician using SPSS (version 25.0, IBM Corp., Armonk, NY, USA). Allocation details will be sealed in sequentially numbered, opaque envelopes. A research assistant not involved in outcome assessment will open the envelopes after baseline testing, just before the first intervention session.

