### Interventions

All groups will train for 8 weeks, three sessions per week, 60 min per session. Each session will include a standardized 10-min warm-up and a standardized 10-min cool-down. Exercise intensity is designed based on the progressive overload, specificity, and neuromuscular adaptation principles of sports coaching, and monitored using a Polar heart rate monitor. Target intensity will gradually increase from approximately 50% of maximum heart rate in week 1 to approximately 60% of maximum heart rate from week 3 onward. There are no differences between the prescribed intensity and the actual training performed, as real-time heart rate monitoring and on-site instructor supervision ensure strict implementation of the intensity protocol. Maximum heart rate will be estimated as 220 minus age. Training instructors will record attendance, heart rate, adverse events, and protocol deviations after each session (Table 2) (21, 22).

**Table 2 tab2:** Standardized warm-up, cool-down, intensity monitoring and safety supervision protocol.

Component	Protocol
Warm-up	Deep breathing for 1 min; dynamic stretching of upper limbs and trunk for 3 min; static stretching of lower-limb muscles for 3 min, focusing on quadriceps, hamstrings, and gluteal muscles; knee rotations and ankle flexion-extension for 3 min.
Cool-down	Whole-body static stretching for 6 min followed by slow walking for 4 min.
Intensity monitoring	Heart rate monitored in real time; intensity progressed from 50% HRmax during early adaptation to 60% HRmax during later weeks; HRmax calculated as 220 - age.
Safety supervision	Sessions supervised by trained instructors; movement quality, fatigue, dizziness, pain, and injury signs monitored continuously.

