### Sample size

The sample size will be estimated using PASS 15.0 software. Knee extensor peak torque will be selected as the primary outcome for sample size calculation. Based on relevant preliminary and published experimental data, the expected mean and standard deviation of post-intervention knee extensor peak torque in the three groups will be used to estimate an effect size of Cohen’s *f* = 0.55. With a two-sided alpha level of 0.05, statistical power of 0.90, and one-way analysis of variance for three-group comparison, the minimum required sample size is 16 participants per group. Allowing for an anticipated dropout rate of approximately 15%, 19 participants will be enrolled in each group, yielding a total sample size of 57 participants (32).

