### Adherence and intervention fidelity

Attendance will be recorded for every session. A participant will be considered adherent if she meets both of the following criteria:

(1) Training frequency adherence: Attendance rate ≥80%; (2) No major protocol deviation: defined as any unapproved change to the intervention content, duration, intensity, or progression that could systematically affect outcome measures, including but not limited to: (a) performing a different Tai Chi form than the 24-form simplified routine, (b) using unstable surfaces or resistance loads outside the prescribed progression in the URT protocol, (c) combining outside structured exercise programmes that interfere with the intervention effect, or (d) persistent incorrect movement patterns that, despite instructor correction, compromise training safety or fidelity. Minor deviations (e.g., occasional missed warm-up exercises, temporary heart rate outside the target zone for <10% of session time) will be recorded but will not automatically classify the participant as non-adherent.

Instructors will follow standardized checklists to ensure intervention fidelity. Heart rate and observations will verify exercise intensity and quality. Missed sessions will be followed up to support continued participation where safe.

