### Statistical analysis

Two analysis sets will be used. The intention-to-treat set will include all randomized participants in their originally allocated groups regardless of adherence or withdrawal. The per-protocol set will include participants who complete the full intervention protocol without major protocol deviations. The primary analysis will be based on the intention-to-treat principle, and the per-protocol analysis will be used as a sensitivity analysis.

Missing data will be handled using multiple imputation when the missingness mechanism is considered missing at random. Baseline knee muscle strength, dynamic balance index values, age, height, and weight will be considered predictor variables for imputation. Five imputed datasets will be generated using a multiple linear regression model in SPSS 25.0. Pooled estimates will be calculated according to Rubin’s rules. If missing data are minimal, complete-case analysis may be reported as a supplementary analysis.

Categorical variables will be expressed as n (%). Normally distributed quantitative variables will be presented as mean ± standard deviation, and non-normal data as median (interquartile range). Normality will be tested with the Shapiro–Wilk test, and variance homogeneity with Levene’s test. For within-group pre–post comparisons, paired t-tests will be used for normally distributed data; otherwise, Wilcoxon signed-rank tests will be applied. Between-group differences will be assessed using one-way ANOVA for parametric data, followed by Bonferroni-adjusted pairwise comparisons when the overall effect is significant. Non-parametric data will be analyzed with the Kruskal–Wallis test, followed by Dunn–Bonferroni pairwise comparisons. Categorical variables will be compared using the chi-square test or Fisher’s exact test. Given three primary outcomes (knee extensor peak torque, knee flexor peak torque, and hamstring-to-quadriceps ratio), a Bonferroni correction will be applied to control multiplicity, with a significance threshold set at *p* < 0.017 (0.05/3). Secondary outcomes are exploratory, a two-sided *p* < 0.05 will be used without multiplicity correction.

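### Table 1 withdraws participants for fewer missed sessions than the adherence rule allows, and lists attendance and compliance, seen only after randomisation, as exclusion criteria

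*Protocol article*

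**What the plan says.** The Interventions section fixes the amount of training: "All groups will train for 8 weeks, three sessions per week, 60 min per session". Three further parts of the article then deal with missed sessions.

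- **Table 1, withdrawal criteria:** "repeated non-attendance (defined as missing two consecutive training sessions or three cumulative training sessions").
- **Table 1, exclusion criteria:** "inadequate training attendance; poor compliance". This row is separate from the withdrawal row.
- **Adherence and intervention fidelity:** the first of two conditions for being adherent is "Training frequency adherence: Attendance rate ≥80"%; the second is the absence of a major protocol deviation. The section adds: "Missed sessions will be followed up to support continued participation where safe".

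On timing, the randomization section says that a research assistant "will open the envelopes after baseline testing, just before the first intervention session". The statistical analysis section says: "The intention-to-treat set will include all randomized participants in their originally allocated groups regardless of adherence or withdrawal". The sample size section adds a margin for losses: "Allowing for an anticipated dropout rate of approximately 15"%, which takes 16 per group to 19, or 57 in total.

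**The concern.** There are two problems, both in rules the article states explicitly.

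First, the withdrawal threshold is stricter than the adherence threshold, so the trial stops training people whose attendance it would otherwise accept. It also works against the stated intention to follow up missed sessions and keep participants in training. Among participants not withdrawn for attendance, nobody can fall below 80%, so the threshold does nothing there; it can classify only those who stop for another reason.

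Second, training attendance and compliance cannot be observed until after allocation, yet they appear as exclusion criteria. Used that way, they would remove randomised participants for behaviour that may depend on the arm, and would move the comparison towards compliers.

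The stake in the first problem is the week-8 outcome. Strength and balance are measured once after baseline, so a withdrawn participant who is not tested contributes no outcome. The article does not say whether she is tested. If she is not, her values in the intention-to-treat analysis come from imputation. The predictors named for it are strength, balance, age, height and weight; attendance, which caused the loss, is not among them.

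**Working it through.** **Thresholds**

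- Sessions: 8 weeks × 3 = 24 (Interventions).
- Adherence: 0.80 × 24 = 19.2, so at least 20 must be attended (20/24 = 83.3%) and four may be missed. The fifth miss fails (19/24 = 79.2%).
- Withdrawal at three misses: attendance can still reach 21/24 = 87.5%.
- Withdrawal at two consecutive misses: attendance can still reach 22/24 = 91.7%. Two separate misses trigger nothing.
- The number of misses at the trigger is therefore two or three, never more, so the best attendance still open to anyone withdrawn is at least 21/24.

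**The plan's own margin**

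16 / 0.85 = 18.8, rounded up to 19 per group, and 3 × 19 = 57. This agrees with the article.

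**How often the rule would act**

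The article gives no rate of missed sessions, so the rate is an assumption. Let p be the probability of missing any one session, independently, and q = 1 − p. A participant avoids withdrawal with no miss, one miss, or two misses that are not adjacent. Of the 24 × 23 / 2 = 276 pairs of sessions, 23 are adjacent, which leaves 253:

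P(withdrawn) = 1 − [q²⁴ + 24·p·q²³ + 253·p²·q²²]

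At p = 0.05: 1 − [0.2920 + 0.3688 + 0.2046] = 0.1345, and 57 × 0.1345 = 7.7 participants.

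The chance of being withdrawn and yet ending with four misses or fewer, had training continued, is P(withdrawn) minus the binomial probability of five or more misses in 24. Everyone with five or more misses is withdrawn, so the subtraction is exact. At p = 0.05: 0.1345 − 0.0060 = 0.1286 (from unrounded values).

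| Assumed miss rate | Withdrawn | Of 57 | Five or more misses | Withdrawn, but would have met 80% |
|---|---|---|---|---|
| 2% | 1.8% | 1.0 | 0.01% | 1.8% |
| 5% | 13.5% | 7.7 | 0.6% | 12.9% |
| 8% | 32.4% | 18.5 | 3.9% | 28.6% |
| 10% | 45.8% | 26.1 | 8.5% | 37.3% |

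Setting P(withdrawn) = 0.15 gives p = 0.053. At that rate the attendance rule alone uses the whole dropout allowance, before any voluntary or safety withdrawal.

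The last column supposes that training had continued. With training ending at the trigger, the share who had already attended 20 sessions is only 0.3%, 2.2%, 4.4% and 5.4% (at most about 3 of 57).

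**If misses cluster within persons**

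With a beta-binomial model and an assumed within-person correlation of 0.1 (400,000 simulated participants), 6.6%, 17.9%, 29.9% and 37.9% are withdrawn at the same four average rates. The share withdrawn who would have met 80% is 4.3%, 10.9%, 16.6% and 19.6%.

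**Timing of the exclusion items**

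Envelopes are opened after baseline testing and just before the first session. Training attendance and compliance therefore do not exist when eligibility is decided. An exclusion based on them can only remove someone already randomised, whereas the intention-to-treat set keeps her.

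**The case against.** A rule for stopping training and a label for adherence serve different purposes, and a strict stopping rule is not a logical contradiction. The primary set keeps all randomised participants, so the withdrawal rule does not contradict the intention-to-treat definition. That is correct and limits the point. What remains is that everyone withdrawn under the rule could still have met the attendance criterion, and that staff are told both to end participation and to support it.

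The exclusion items might mean anticipated poor attendance, since they follow items on leave, internship and transfer. That reading is strained: the wording refers to attendance and compliance themselves, and the inclusion criteria already cover ability and willingness to complete training.

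The loss of week-8 data is argued from silence in a condensed article, and the flow diagram and schedule are not available here. This stands, so the missing-data harm is conditional. The bias towards compliers likewise arises only if the exclusion row is applied over the intention-to-treat definition.

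The sizes run from negligible to severe because no rate of missed sessions is given. Under clustering, the share withdrawn who would have met 80% is about half the independent figure at a 10% rate (19.6% against 37.3%), though higher at 2% (4.3% against 1.8%). These are scenarios, not forecasts; the conflict between the rules does not depend on them.

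**Conclusion.** The concern holds and should be fixed. The mismatch of thresholds follows exactly from the article: four misses of 24 are acceptable for adherence, while three in total or two in a row lead to withdrawal. The exclusion items are misplaced because they describe behaviour after allocation, and applying them as written would conflict with the intention-to-treat set.

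The number affected rests on the assumed miss rate. Between 2% and 10%, withdrawal ranges from 1.8% to 45.8% with independent misses and from 6.6% to 37.9% with the clustering assumed here. Very rare absence would make the loss small. Damage to the primary analysis depends further on whether withdrawn participants are tested at week 8.

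**What to change.** 1. Delete the attendance and compliance items from the exclusion row of Table 1.
2. Replace attendance-based withdrawal with a statement that missed sessions count as non-adherence or as stopping training, not as leaving the study. Set the threshold at the fifth missed session, in line with the 80% rule.
3. Use that threshold only to define the per-protocol set, and say so in the statistical analysis section, whose present definition does not cite the 80% figure.
4. State that every randomised participant is invited to the week-8 strength and balance tests whatever her attendance, and that these values enter the intention-to-treat analysis.
5. Leave the safety-based withdrawal criteria unchanged.

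The cost is a protocol amendment through the ethics committee and attendance at an already scheduled test visit by those who stop training. It is best done before sessions begin to be missed; recruitment is planned to start in May 2026.
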